**Fig. 1 Fig1:**
[figure not shown]
Clinical practice guideline. Abbreviations are defined in Table 1

**Table 1 Tab1:** Abbreviations used in the clinical practice guideline

General preventive measures/recommendations prior to orthodontic treatment with fixed appliances	Abbreviation
1. The mouth should be free of plaque, caries, and gingivitis before starting orthodontic treatment	GM1-7
2. Explanation of the current oral health situation	
3. Advice regarding tooth-friendly nutrition and oral hygiene	
4. Oral hygiene instruction, evaluation of psychomotor skills and, when appropriate, advise brushing with powered tooth brush	
5. Topical fluoride varnish on visible/present white spots	
6. Tooth brushing with toothpaste containing fluoride (1,450 ppm) twice daily	
Start treatment when oral health status is appropriate	ST
Postpone treatment until specific requirements are met, as stated in the general measures/recommendations, including appropriate oral hygiene level and lower risk of caries due to decreased sugar intake	PT
Specific preventive measures/recommendations during orthodontic treatment with fixed appliances	
Use of a toothpaste containing fluoride (1,450 ppm) twice daily	HF
Removal of the wires, cleaning/polishing the teeth, and applying topical fluoride varnish	FV
Appropriate dietary and oral hygiene advice	DA
Letter to the (parents of the) patient including an explanation of the problem and a copy to the GDP	LP1
Letter to the (parents of the) patient describing visible carious damage to the teeth, including an explanation of the problem and a copy to the GDP	LP2
Letter to the (parents of the) patient regarding debonding (removal of all fixed appliances) with a copy to the GDP	LP3
Debonding (removal of all fixed appliances without placement of permanent retention)	DB

The CPG has been converted into a CDSS, which is to be integrated in the electronic patient files (EPFs) of the participating practices. For each patient, the program will automatically lead the clinician through the questions needed to determine the patient’s caries risk. Upon input of the answers, the program will display the recommended preventive strategy to be followed, and will store all of this information in the EPF.

The control group will not receive any intervention. Practices in the control arm of the trial will use their standard WSL preventive measures. Registration in the EPF will be performed in accordance with the medical record keeping guidelines of the Dutch Dental Society [12].

Pre- and post-treatment digital intra-oral photographs will be taken in both the intervention and the control practices. The photographic setting will be standardized in terms of lighting conditions and camera positioning to ensure validity of the WSL measurements [13].

### Implementation program

The CPG will be implemented using a multifaceted intervention strategy (See Table 2.) The implementation process will be evaluated in only a limited number of practices, since this is not the primary aim of the study. First, the CPG will be disseminated by mail to the participating orthodontists in the intervention arm, together with instructions for using the CPG. One week later, the principal investigator will make an educational outreach visit to the participating practices in the intervention arm, with the goals of further explaining the recommendations in the CPG along with their rationale, and of demonstrating the use of the CDSS integrated in the EPF. Clinicians will also be provided instructions regarding the following:Evaluation of oral health in terms of the presence or absence of cavities, restorations, or WSLsEvaluation of oral hygiene level in terms of plaque index [14], using pictures of patients with varying plaque levelsHow to appropriately explain the patient’s current oral health situation, and to give appropriate advice regarding tooth-friendly nutrition and oral hygieneHow to give appropriate oral hygiene instructionHow to correctly apply fluoride varnish (Duraphat 50 mg/mL for dental use) after wire removal and tooth polishing

**Table 2 Tab2:** Implementation strategy

	Type of intervention
0	Dissemination of the CPG together with instructions for use
1 week	Educational outreach visits
5 weeks	Monitoring and feedback regarding use of the CPG through computerized patient records

The practices in the intervention group will also be given patient information folders containing the recommended oral hygiene and dietary instructions, together with the recommended letters that are to be sent to the parents and the general dentists in cases of poor oral hygiene. After 5 weeks, the number and types of preventive actions registered in the EPF will be extracted from the software and analyzed. This information will be used to give feedback to the participating practices regarding guideline adherence. For this purpose, a second visit by the principal investigator is planned, during which the practitioners will have the opportunity to discuss potential problems. This will provide insight into the problems and barriers encountered in the specific practice that may be hindering adequate guideline implementation.

### Outcome parameters

#### Primary outcome

The primary outcome measure is the proportion of patients treated with full fixed orthodontic appliances who develop at least one new or enlarged WSL after 6–9 months of treatment with fixed appliances, and at the completion of treatment, when using the CPG for WSL prevention as compared to usual preventive measures.

#### Outcomes for implementation process evaluation

The process of CPG adoption in routine clinical orthodontic practice will be assessed in terms of the following factors:Professionals’ attitudes towards utilizing the CPG for WSL prevention, measured using a questionnaireProfessionals’ compliance with the key recommendations in the CPG for WSL prevention, measured by auditing the EPFPatients’ views regarding the provided preventive care, measured using a questionnaire.

### Measurements

#### Primary outcome

The number of WSLs per patient will be determined by examination of maxillary incisors and canines, mandibular canines, and maxillary and mandibular premolars by two independent observers, who will be blinded to the patient’s intervention status. Standardized pre-treatment intra-oral photographs (T0) will be compared with intra-oral photographs taken after 6–9 months of treatment (T1), and after completion of treatment with fixed orthodontic appliances (T2). If comparison of the T0 photographs to the T1 and T2 photographs reveals an identical white spot on all three images, it will be considered a developmental white spot and will not be counted as a WSL. For each patient, the total number of new and enlarged WSLs will be registered. The proportion of patients showing new or enlarged WSLs will be determined for each group.

A pilot study using pre-and post-treatment intra-oral pictures of 150 patients from three orthodontic practices (50 patients per practice) demonstrated an inter-observer agreement of 0.6, which is considered acceptable. However, this agreement varied among the practices, mainly due to the quality of the intra-oral photographs. In the retrospective pilot study, the photographic technique was not standardized in terms of lighting and camera positioning. For the presently described prospective trial, lighting and camera positioning will be standardized, which will likely lead to better agreement. An earlier *in vitro* study measured artificially induced WSLs on extracted maxillary incisors that were photographed at different angles using standardized techniques. Their results showed non-significant interobserver differences in the surface measurements of WSLs of less than 0.1 mm [13].

Prior to its dissemination in the trial, the questionnaire’s readability and content validity will be tested in a sample of ten orthodontically treated patients at the academic Department of Orthodontics of the Radboud University Medical Center. Patients will be asked to complete the questionnaire in the presence of the main investigator, enabling us to gain more insight regarding parts of the questionnaire that may be difficult, unclear, or incomplete. Adjustments will be made if needed.

### Data collection

The data collection and timeframe are given in Table 3.

**Table 3 Tab3:** Data collection and study timeframe

Months	
1–2	14 orthodontic practices included
	Collection of baseline data (photographs of 50 treated patients and baseline questionnaire)
3	Assignment to intervention or control arm
	Information meeting
	Dissemination of CPG and educational outreach visit 1 week later*
	Professional questionnaire*
4–6	Start inclusion of patients with informed consent
10–12	Patient questionnaire
	EPF registrations
10–15	Intra-oral photographs (6–9 months into treatment)
22–30	Registration of compliance in electronic patient files*
	Intra-oral photographs
	Professional questionnaire*

* For intervention group only

#### Baseline data

After giving their informed consent to participate, orthodontists will be asked to complete a questionnaire including personal and practice information. They will also be asked about the usual preventive strategies applied in their practice. Additionally, we will evaluate pre- and post-treatment intra-oral pictures of the last 50 patients who completed orthodontic treatment with fixed appliances at each practice, to obtain the baseline incidence of WSLs at each participating orthodontic practice.

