### Randomization

Utilization of both the CPG and the usual preventive measures within the same practice would inevitably result in some control patients receiving some CPG-recommended care, which would dilute the effect of the intervention. To prevent such contamination of interventions between study groups, we will perform cluster randomization at the level of practices rather than individuals. Using a software program, practices will be assigned to either the *intervention arm* or the *control arm* by an independent statistician who is not familiar with the practices.

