#### Sample size and power calculation

We have calculated the number of patients needed to detect a difference in the proportions of patients with newly developed or enlarged WSLs between the intervention group using the CPG and the control group using standard preventive strategies. Earlier studies show that more than 1 in 4 orthodontic patients develop at least one new WSL during the course of orthodontic treatment [3]. Assuming a power of 80 %, a significance level of 5 %, and an ICC of 0.05 to correct for clustering, we calculated that we must include a minimum of 14 orthodontic practices with 50 patients per practice to detect a medium effect size of 0.4 for reduction in newly developed WSLs. The effect size was arbitrarily chosen, as no previous data establish what would constitute a clinically relevant change. The study is powered to detect an effect of 15 % absolute reduction in prevalence of WLS, under the assumptions specified above. Assuming a drop-out rate of 20 %, we plan to recruit a total of 60 patients per participating practice, resulting in a total inclusion of 840 patients. In a regular orthodontic practice, about 40 patients receive full fixed appliances each month. To account for an overestimation of the number of patients to potentially be included in the practices, we will have a 2-month inclusion period.

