#### Primary outcome

To account for the data clustering (in orthodontic practices), a multilevel logistic regression analysis will be applied on patient data, using the presence of new WSLs at T2 (yes/no) as the outcome, and the type of intervention (CPG or usual preventive measures) as the predictor. In this model, the regression coefficient of the predictor “intervention versus control” indicates the effectiveness of the intervention. Given the expected distribution of outcomes, we anticipate the use of binomial logistic regression with a logit link function. We will also examine the influences of age at start of treatment, gender, patients’ opinion on preventive measures, patients’ initial oral health status, patients’ initial oral hygiene status, and patients’ initial sugar intake on the primary outcome measure, by including these factors one by one as predictors in the regression model. These covariates are known to potentially influence the development of WSLs during orthodontic treatment [3, 9]. We do not anticipate a high number of missing values. However, in the event that we do have high numbers of missing values, we will apply a multiple imputation method prior to the planned analyses.

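### The practice-level baseline WSL incidence, measured before allocation, is left out of the primary model: precision may be lost, but there is no bias

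*Protocol article*

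**What the plan says.** Under Baseline data, pre- and post-treatment pictures of the last 50 patients to complete fixed-appliance treatment are evaluated at every practice, "to obtain the baseline incidence of WSLs at each participating orthodontic practice". Table 3 (Data collection) puts this in months 1–2 and "Assignment to intervention or control arm" in month 3. The measure is thus available before allocation.

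Under Statistical analysis, Primary outcome, the model is a multilevel logistic regression of new WSLs at T2, with "the type of intervention (CPG or usual preventive measures) as the predictor". Age, gender, opinion on preventive measures, initial oral health, initial oral hygiene and initial sugar intake are then examined "by including these factors one by one as predictors in the regression model". All six describe the patient. The practice's own baseline incidence is not among them, and no other section gives it a role in the analysis.

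The Randomization section says that software is used and that the assignment is made "by an independent statistician who is not familiar with the practices". It does not say whether the allocation is restricted in any way.

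**The concern.** In a cluster trial with 14 practices, most of the error in the treatment comparison comes from differences between practices. A pre-allocation measurement of the same outcome in the same practices is a natural covariate for that error, and the plan already pays for its collection. This is more than silence on a detail: the analysis section writes out the model and names its covariates, and this one is absent. If practice rates persist over time, the treatment effect will be estimated with a wider interval than the data allow. Adding the covariate only after a baseline gap between the arms has been seen would be a post hoc choice.

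**Working it through.** **Inputs from Sample size and power calculation:** "Assuming a power of 80 %, a significance level of 5 %, and an ICC of 0.05 to correct for clustering"; 14 practices with 50 patients each; effect size 0.4; 15-point absolute reduction; control rate about 25 %. Assumed here: a two-sided test, seven practices per arm, and 25 % versus 10 % as the reading of the 15-point reduction.

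**Reproducing the plan's figure**
- Cohen's h for 25 % versus 10 % is 0.404, so the two effect statements agree.
- Individually randomised size for 25 % versus 10 %: 100 per arm.
- Design effect: 1 + (50 − 1) × 0.05 = 3.45.
- Total: 2 × 100 × 3.45 = 690; 690/50 = 13.8, rounded up to 14 practices (700 patients). The stated size reproduces without baseline adjustment.

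**Power without adjustment**
- SE = √[(0.25 × 0.75 + 0.10 × 0.90) × 3.45/350] = 0.0523.
- Effect/SE = 0.15/0.0523 = 2.868.
- Normal approximation: Φ(2.868 − 1.960) = 82 % (81 % with a pooled-variance formula). Noncentral t on 12 df: 75 %.

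**How much of the error lies between practices**
- Share of the variance of a practice mean: m × ICC/[1 + (m − 1) × ICC] = 2.5/3.45 = 0.725.

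**Power with adjustment.** Let c be the correlation over time between a practice's true historical and trial rates. The article does not give c, so it is an assumption. With 50 patients in each period, the correlation between observed rates is r = c × 0.725, and the variance of the comparison is multiplied by 1 − r². One degree of freedom is spent (12 to 11).

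| c (assumed) | r | Variance removed (r²) | Design effect | Power, t on 11 df |
|---|---|---|---|---|
| 0 | 0 | 0 % | 3.45 | 74 % |
| 0.2 | 0.14 | 2 % | 3.38 | 75 % |
| 0.3 | 0.22 | 5 % | 3.29 | 76 % |
| 0.5 | 0.36 | 13 % | 3.00 | 80 % |
| 0.6 | 0.43 | 19 % | 2.80 | 83 % |
| 0.8 | 0.58 | 34 % | 2.29 | 89 % |

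Against 75 % unadjusted, break-even is at a correlation of about 0.2. Below that, the loss is under one point. These figures work on the scale of practice proportions and approximate the planned logistic model.

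**Chance imbalance, for scale**
- Between-practice SD at 25 %: √(0.05 × 0.25 × 0.75) = 9.7 points.
- SD of the difference in true baseline rate between two arms of seven: 9.7 × √(2/7) = 5.2 points.
- Probability of a gap above 5 points: 33 %. Above 7.5 points, half the target effect: 15 %.

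**The case against.** The strongest reply is that nothing here is an error. A multilevel model with arm as its predictor is valid, randomisation protects it from bias on average, and the sample size stands without adjustment. That is right, and it limits the point to efficiency.

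The size of the gain is also open. Several statements in the article point to a modest correlation:
- The pilot (Measurements, Primary outcome) found agreement of 0.6 on retrospective photographs, varying among practices with photographic quality.
- The historical patients are the last 50 completers, with no mention of the trial's eligibility criteria.
- Treatment lasts 2 to 2.5 years, so the two sets of outcomes are years apart.
- Intervention practices change their prevention regime.

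These are reasons to show the low end of the range. They are not reasons to omit a covariate whose worst case costs under one point of power.

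Four stronger readings are tempting, and the document does not support them:
- A reader might infer that chance imbalance between the arms is a further threat to the result. The 5.2-point SD is the same between-practice variance that the ICC of 0.05 puts into the sample size and that the multilevel model carries into the standard error.
- A reader might infer that the allocation ignores the baseline rate. The article does not say whether allocation is restricted, and a condensed article may leave that to the full protocol.
- A reader might take this as the only variable bearing on practice differences. Usual preventive strategies are also recorded for each practice before allocation, and the patient-level covariates may explain part of the variation through case mix.
- A reader might think that the data are already in hand. Trial status reports six recruited practices with baseline data analysed; eight were still being recruited.

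**Conclusion.** The point holds as a matter of precision. The plan measures a practice-level baseline of its own outcome before allocation and specifies a primary model that does not use it. The primary analysis is neither biased nor invalid, and the sample size is not wrong on this account.

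The possible gain runs from nothing (74 % against 75 %) to about 14 points (89 % against 75 %) as the assumed correlation goes from 0 to 0.8. It becomes material from about 0.5 upward. The 75 % starting point comes from using t on 12 df; by the normal approximation the unadjusted power is already about 82 %, so part of the apparent recovery reflects the small number of practices and not the missing covariate. The figures also rest on seven practices per arm, 50 evaluable patients each, a two-sided test and 25 % versus 10 %.

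**What to change.** In Statistical analysis, Primary outcome, prespecify the practice's baseline WSL proportion (from its 50 historical patients) as a fixed practice-level covariate in the primary multilevel logistic model, and keep the model without it as a sensitivity analysis. The cost is a sentence in the analysis section and one practice-level degree of freedom (12 to 11). No new data are needed beyond the planned collection, although that collection still has to be completed at the practices not yet recruited.

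Optionally, where practices are not yet allocated, the allocation could be balanced on the same proportion. If the full protocol already restricts the randomisation, the analysis section should say so and account for it.

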#### Intra-oral digital photographs

For all included patients, three intra-oral digital photographs will be taken (Fig. 2) at each of three time points: T0, pre-treatment before placing fixed appliances; T1, 6–9 months into treatment with fixed appliances; and T2, end of treatment with fixed appliances. Intro-oral photographs will be taken after polishing all tooth surfaces, and utilizing standardized lighting conditions and camera positioning. The timing for T1 was chosen because this is when a radiograph is usually taken to diagnose possible root resorption. Combining the radiographic procedure with taking intra-oral digital photographs reduces the interference with routine practice and the additional burden to the patient. In most orthodontic practices, it is standard procedure to take intra-oral photographs before (T0) and after treatment (T2); therefore, these photographs do not represent an additional burden to either the patient or the orthodontist. An orthodontic treatment usually lasts about 2 to 2.5 years.

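### Table 3 places the end-of-treatment (T2) photographs at study months 22–30, but the article's own inclusion window and treatment duration put them at about months 28–36

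*Protocol article*

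**What the plan says.** **When T2 occurs.** The section on intra-oral digital photographs defines the last time point by an event: "T2, end of treatment with fixed appliances". It applies to all included patients. The same section gives the expected duration: "An orthodontic treatment usually lasts about 2 to 2.5 years".

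**When it is scheduled.** Table 3, titled "Data collection and study timeframe", runs in study months. Months 4–6 carry "Start inclusion of patients with informed consent". Months 10–15 carry "Intra-oral photographs (6–9 months into treatment"), which is T1. The last row, months 22–30, carries "Registration of compliance in electronic patient files", the final intra-oral photographs and the closing professional questionnaire. The section on professionals' attitude places that questionnaire at the end of the trial.

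**How T2 is used.** The primary outcome is defined at 6–9 months and at completion of treatment. The multilevel logistic model in the statistical analysis section takes new lesions at T2 as its outcome. On missing data that section says: "We do not anticipate a high number of missing values". Multiple imputation is to be used if the number proves high. The sample size section allows for 20 % drop-out.

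**The concern.** The schedule for the last photographs and the stated length of treatment cannot both be right. Most of the months 22–30 window falls before a patient with the usual treatment length could have finished, and most of the period in which patients would finish falls after it. Because the primary model rests on T2, a study run to this timetable could reach its last scheduled month with many patients still wearing appliances and no outcome for the main analysis. The article does not say what would then happen to those patients. The 20 % allowance and the expectation of few missing values do not provide for it.

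**Working it through.** **Inputs**

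- Inclusion: study months 4–6 (Table 3). The sample size section says "we will have a 2-month inclusion period".
- T1: 6–9 months into treatment, scheduled for months 10–15 (Table 3).
- T2: end of treatment, usually 24–30 months after the start (section on intra-oral digital photographs), scheduled for months 22–30 (Table 3).

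**Step 1: confirm the table's clock.** Window = (first inclusion month + shortest interval) to (last inclusion month + longest interval). For T1: 4 + 6 = 10 and 6 + 9 = 15. Table 3 states 10–15, so the rule reproduces that row exactly.

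**Step 2: apply the same rule to T2.** 4 + 24 = 28 and 6 + 30 = 36, so months 28–36. Table 3 states 22–30. The difference is six months at each end, and the two windows share only months 28–30.

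**Step 3: read the table backwards.** 22 − 4 = 18 and 30 − 6 = 24. The T2 row corresponds to 18–24 months of treatment, against the stated 24–30.

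**Step 4: illustrate the size if month 30 were a cut-off.** Let S be the entry month and D the treatment duration. The share with T2 by month 30 is P(S + D ≤ 30). The article gives no distribution for either, so the shapes below are assumptions. With S uniform over 4–6 and D uniform over 24–30, the share is E[(6 − S)/6] = (6 − 5)/6 = 1/6, or 140 of 840 patients. For a normal duration with mean μ and SD σ it is E[Φ((30 − S − μ)/σ)].

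| Assumed duration (months), entry uniform over 4–6 | T2 by month 30 | T2 after month 30 |
|---|---|---|
| Uniform 24–30 | 17 % | 83 % |
| Normal, mean 27, SD 3 | 26 % | 74 % |
| Normal, mean 27, SD 4 | 31 % | 69 % |
| Normal, mean 24, SD 4 | 60 % | 40 % |

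The last row is favourable to the plan: it centres durations on the lower edge of the stated range. A more peaked shape is less favourable: a triangular distribution on 24–30 with mode 27 leaves 93 % after month 30.

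**Step 5: check sensitivity to how months are counted.** If month 4 begins at 3.0 elapsed months, entry runs over 3–6, or over 3–5 with a two-month inclusion period. The uniform duration then gives 25 % or 33 % by month 30. The favourable case (mean 24, SD 4) gives 64 % or 69 %, leaving 36 % or 31 % without T2. Every case tried exceeds 20 %.

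**Step 6: illustrate the effect on power.** The planned size reproduces first. With 25 % against 10 % (the 15-point reduction, taken from the one-in-four control rate), ICC 0.05 and 50 patients in each of 14 practices, the design effect is 1 + 49 × 0.05 = 3.45. The effective size per arm is 350/3.45 = 101, and power is 81 %. If only the 140 patients of the uniform case were analysed (10 per practice), the design effect is 1 + 9 × 0.05 = 1.45, the effective size per arm is 70/1.45 = 48, and power is about 49 %, before any other drop-out.

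**The case against.** The strongest reply is that Table 3 is a planning timetable. It states no cut-off, and nothing in the article excludes later photographs. The operative definition of T2 is event-based and covers all included patients, so photographs could simply be taken when appliances come off. The trial status section suggests that the calendar is nominal: eight of the 14 practices, which the table places in months 1–2, were still being recruited after baseline data had been analysed. This part of the reply stands. A reader might infer that collection closes at month 30 and that most primary outcomes will be lost. The article does not support that: the loss follows only if the window is enforced, and the T1 part of the primary outcome (months 10–15) is untouched either way.

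A reader might also infer that the missing patients would differ by arm, because the guideline can postpone treatment or lead to early removal of appliances. That is possible but not shown. No rates are given, the article does not say whether postponement falls before or after inclusion, and early removal brings T2 forward rather than losing it.

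The plan also provides for multiple imputation if missingness is high, so it is not without a response. The details of that imputation can be left to an analysis plan that is not shown.

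The reply does not remove the contradiction. Months 22–30 is the last row of the study timeframe and also holds the end-of-trial questionnaire. No later collection is stated, and nothing says how patients still in treatment at month 30 are followed.

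**Conclusion.** The inconsistency is established by addition and needs no distributional assumption: about months 28–36 from the stated inclusion and duration, against 22–30 in the table. It matters because the primary model uses T2 alone.

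The consequence is conditional. If month 30 were enforced, a large share of T2 outcomes would be missing, illustratively about 40–83 % with entry spread over months 4–6, against the 20 % allowed. Those percentages rest on a hard stop and on assumed entry and duration distributions; the article says only that the duration is usual and approximate. They are not a forecast of the missing rate. The article does not settle whether the table or the duration sentence is wrong.

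**What to change.** Reconcile Table 3 with the section on intra-oral digital photographs. If the stated duration of 2 to 2.5 years stands, change the T2 row and the end of study to about months 28–36. If months 22–30 reflects the true expectation, correct the duration sentence instead.

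In either case, state that T2 is collected at each patient's appliance removal, that the closing date is the same in both arms, and that month 30 is not a cut-off. Say what happens to patients still in treatment at closure, since some treatments will outlast the usual range.

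The cost is an amendment and, if the stated duration stands, about six more months of data collection (36 − 30). The article says that most practices already take photographs at the end of treatment as standard procedure, so the added burden should be small.
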